### Sample size calculation, randomization and statistical analysis

The sample size has been calculated considering the primary outcome, the daily mean concentration of coffee-derived plasma circulating phenolic metabolites, and according to Lenth [55]. Considering the lack of literature dealing with this outcome, the AUC of dihydrocaffeic acid-3′-sulfate, one of the most representative coffee-derived phenolic metabolites [56], has been used for sample size calculations. Keeping a 80% power and an α of 5%, and considering data from Stalmach et al. [56], 15 subjects will have to complete an acute intervention to detect a change of 600 nmol/h/L^-1^ in dihydrocaffeic acid-3′-sulfate plasma concentration with a standard deviation of 870 nmol/h/L^-1^. A total of 21 subjects will be recruited to allow for dropouts and for nonparametric statistical analysis (15% additional subjects required). Power calculation will be retrospectively calculated for the secondary cardiometabolic outcomes (post hoc sample size calculation). Once the volunteers have been recruited, a randomization list will be generated using a randomized block design by means of Random Number Generator Pro (Segobit Software). This list will be made by a colleague not involved in subject enrollment, and using a numbered sequence in sealed, opaque envelopes. It will be blind for the Principal Investigator (PI) and volunteers.

Before any comparison is performed, the normality of each variable will be evaluated to choose the most appropriate statistical test. If normally distributed, data will be expressed as mean ± standard deviation and analyzed using general linear models for repeated measures with post hoc comparisons. If data are not normally distributed, they will be reported as median and interquartile range and the Friedman test with post hoc pairwise comparisons will be performed. Multivariate analyses will be carried out to understand individual responses to coffee consumption on the basis of metabolite production. All the analyses will be carried out using SPSS 23.0 (IBM Corp., Armonk, NY, USA). *P* value <0.05 will be regarded as statistically significant.

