**Discussion:**

Results will provide information on the bioavailability of the main groups of phytochemicals in coffee and on their modulation by the level of consumption. Findings will also show the circulating metabolites and their bioactivity when coffee consumption is substituted with the intake of cocoa-based products containing coffee. Finally, the effect of different levels of 1-month coffee consumption on cardiometabolic risk factors will be elucidated, likely providing additional insights on the role of coffee in the protection against chronic diseases.

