## Methods/Design

### Objectives

With ultimate aim of studying the bioavailability of coffee/cocoa bioactive compounds and their effects in cardiometabolic health, the objectives of this intervention will be:(i)ssessing the bioavailability of the four main groups of phytochemicals in roasted coffee (methylxanthines, phenolic compounds, trigonelline, and diterpenes), its modulation by the level of consumption, and establishing the daily average concentration of coffee-derived plasma circulating metabolites;(ii)investigating the effect of different levels of coffee consumption on cardiometabolic risk factors;(iii)evaluating circulating metabolites and their putative bioactivity when substituting coffee consumption with the intake of cocoa-based products containing coffee.

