### Measurements

The primary selected endpoint of the study is the quantification of the daily mean concentration of coffee-derived plasma circulating phenolic metabolites, whereas the study of the bioavailability of other coffee-derived circulating bioactives, the bioavailability of cocoa-derived circulating phytochemicals, and the assessment of cardiometabolic markers will be considered secondary endpoints.

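### Retrospective power for the secondary cardiometabolic outcomes has no target difference fixed for it; at the observed effect it only re-expresses the P value

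*Protocol article*

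**What the plan says.** Under Sample size calculation, randomization and statistical analysis, the protocol article sizes the trial on one surrogate for the primary outcome, the AUC of a single phenolic metabolite. The inputs are "Keeping a 80% power and an α of 5"%, the aim "to detect a change of 600 nmol/h/L^-1^ in dihydrocaffeic acid-3′-sulfate plasma concentration", and the spread "with a standard deviation of 870 nmol/h/L^-1". The result is that "15 subjects will have to complete an acute intervention", with 21 recruited.

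For the cardiometabolic outcomes the same section offers only this: "Power calculation will be retrospectively calculated for the secondary cardiometabolic outcomes (post hoc sample size calculation". It names no target difference, SD or detectable difference for any of these markers. It does not say which effect size the retrospective calculation will use, or how the result will be used.

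The outcomes concerned are secondary: under Measurements, "the assessment of cardiometabolic markers will be considered secondary endpoints". They also carry objective (ii), "investigating the effect of different levels of coffee consumption on cardiometabolic risk factors", and the abstract's Discussion expects that "the effect of different levels of 1-month coffee consumption on cardiometabolic risk factors will be elucidated".

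The planned tests are a repeated-measures general linear model with post hoc comparisons or, for non-normal data, the Friedman test with pairwise comparisons, at P<0.05.

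**The concern.** Power is a property of a design at an effect size chosen independently of the result. If the effect size is the one just observed, power becomes a function of the test statistic, and so of the P value. It then carries no information beyond P.

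This matters for reading the non-significant markers. The trial was sized on a metabolite AUC, the cardiometabolic list is long (14 cytokines and chemokines alone under Inflammatory markers), and non-significant results are likely for some of them. The useful question for each is whether the data exclude a difference worth caring about or are too imprecise to say. Observed power cannot answer that, and it is the only aid to interpreting these results, beyond the test itself, that the section names.

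**Working it through.** **1. The plan's own figure.** Inputs: change 600, SD 870 (taken as the SD of within-subject differences, which the text does not say), power 80%, α 5% (sidedness not stated).
- Normal approximation, two-sided: n = [870 × (1.960 + 0.842) / 600]² = 16.5, so 17.
- Paired t-test, noncentral t: one-sided gives 15 (power 0.81); two-sided gives 19 (power 0.70 at 15).

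The stated 15 is thus reproduced with a one-sided t-test. This concerns the primary outcome only. There is no corresponding figure to reproduce for the cardiometabolic outcomes.

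**2. Observed power against P, paired t contrast.** With n completers, observed statistic t and critical value t* (two-sided 5%, n−1 df), observed power = Pr(|T| > t*), where T is noncentral t with n−1 df and noncentrality equal to the observed t. P and n fix t, so they fix the power. Repeating the calculation with an SD of 1, 10 or 100 gives identical values.

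| P | n=15 | n=18 | n=21 |
|---|---|---|---|
| 0.01 | 0.79 | 0.78 | 0.77 |
| 0.05 | 0.51 | 0.51 | 0.51 |
| 0.10 | 0.38 | 0.38 | 0.38 |
| 0.30 | 0.17 | 0.17 | 0.17 |
| 0.50 | 0.10 | 0.10 | 0.10 |
| 0.80 | 0.06 | 0.06 | 0.06 |

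The 18 is an assumption, midway between the 15 required and the 21 recruited.

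**3. The three-treatment F test.** With 2 and 2(n−1) df, sphericity assumed, and noncentrality 2 × observed F, P=0.05 gives 0.58, P=0.10 gives 0.46 and P=0.50 gives 0.16 at each of the three sample sizes. For the Friedman test the correspondence with P is approximate.

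**4. What it cannot separate.** Illustration with assumed values: n=18, P=0.30 (t = 1.069), a difference of interest of 5 units, t* = 2.110.
- SD of differences 4: SE = 4/√18 = 0.94; estimate 1.069 × 0.94 = 1.0; 95% CI −1.0 to 3.0, which excludes 5. Observed power 0.17; power at 5 units 0.999.
- SD of differences 15: SE = 15/√18 = 3.54; estimate 1.069 × 3.54 = 3.8; 95% CI −3.7 to 11.2, which includes 5. Observed power 0.17; power at 5 units 0.27.

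The two situations call for opposite conclusions about 5 units, and observed power is the same in both. The CI separates them, and so does power at a fixed target.

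A simulation at n=18 agrees. Among non-significant results, median observed power was 0.09 (interquartile range 0.06 to 0.17) with no true effect and 0.17 (0.08 to 0.30) with a true effect of 0.3 SD. The maximum was about 0.51 in both.

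**5. What can be stated in advance.** Solve the noncentral-t power for 0.80, in SDs of the within-subject difference:

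| Completers | One contrast, two-sided 5% | Three contrasts, Bonferroni (5%/3 each) |
|---|---|---|
| 15 | 0.78 | 0.93 |
| 18 (assumed) | 0.70 | 0.83 |
| 21 | 0.64 | 0.76 |

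The Bonferroni column is an assumption, since the article does not name the post hoc adjustment.

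**The case against.** The strongest objection is that the text never says the observed effect will be used. The bracketed phrase about a post hoc sample size could mean taking the observed SD and a relevant difference chosen separately. Power computed that way does not re-express P, as step 4 shows (0.999 against 0.27 at the same P). This stands as a limit on certainty about the reading. It does not rescue the plan, because no such difference is fixed anywhere in the article, and one chosen after the data are seen would be open to the result.

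Three stronger readings are tempting, and the document does not support them.
- A reader might infer that every significant marker would be declared adequately powered. The figures contradict this: P=0.05 gives about 0.51 and P=0.01 about 0.78 at n=18, both below 80%. Only the statement about non-significant results holds.
- A reader might infer that the sponsor intends to explain away null results by low power. The article gives the calculation no role in any test or conclusion, so that use would be a guess.
- A reader might infer that objective (ii) goes unanswered. It is still tested by the general linear model or the Friedman test with post hoc comparisons.

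It is also fair to say that the choice to report confidence intervals is commonly left to an analysis plan. Their absence from the article is not the point here. The point is that the article commits to a calculation that cannot do their work.

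**Conclusion.** The concern holds in a bounded form. The article commits to a retrospective power calculation without an effect size. On the plain reading it repeats the P value on another scale: every non-significant marker will show power below about 0.51 (paired t contrast) or 0.58 (three-treatment F test), whatever its precision. The correspondence is exact for the t and F tests and approximate for Friedman. The conclusion rests on reading the sentence as power at the observed effect, the only effect available without a post hoc choice. What is affected is the interpretation of secondary outcomes. The change is worth making before analysis but is not critical to the trial.

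**What to change.** Delete the retrospective calculation. For each secondary cardiometabolic outcome, report the between-treatment difference with a 95% CI, and judge a non-significant result by which differences the interval excludes. State in advance the difference detectable with 80% power, using the table in step 5 and saying whether the pairwise comparisons are adjusted and how many completers are assumed. Converting these to mmHg, mmol/L and so on needs an external or baseline SD of the within-subject difference for each marker, which the document does not give.

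The cost is one replaced sentence, with no additional data or participants. The only downside is that the stated detectable differences will look large.

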### Confidentiality of data

Each participant will be assigned to a unique code provided by the PI, so that all personal information, including questionnaire information and samples, will be confidential. Information will be collected exclusively by the PI (or the specialized staff officially involved in the study) and will be stored in a dedicated non-web-connected computer. Sample codification will be hidden to the researchers analyzing the samples (single-blind study). Recruited volunteers will sign an authorization to the use of personal information and data. The identity of the participants will not be revealed in any published data or in presentation of the information obtained as a result of this study. All the data collected for this study will be treated as confidential. All biological specimens will be destroyed after the analysis, as indicated in the informed consent given to the volunteers and according to the procedures of the University of Parma.

## Discussion

There is growing evidence that regular coffee consumption is associated to several beneficial effects on health. However, research has emphasized how differences in the number of cups consumed on a daily basis affect the prevalence of cardiometabolic disorders [15, 57–63] and biomarkers of cardiometabolic risk [15, 61, 64]. There is a linear inverse dose-response relationship between coffee consumption and diabetes, and every additional cup of coffee in a day is associated with a 5% to 10% lower risk of new-onset disease [6, 60, 65]. In the case of CVD, a non-linear U-shaped curve links coffee consumption and CVD risk, with the largest risk reduction observed at a level of about three cups/day, although high rates of variability have been observed [59, 66, 67]. These difficulties in defining the required coffee intake to promote cardiometabolic health make dietary recommendations for coffee consumption almost impossible [12]. Thus, randomized trials addressing the impact of coffee dose on markers of cardiometabolic risk are needed [6, 15, 16].

Intervention studies considering coffee dosage are scarce, and the biological actions underlying the preventive effects of coffee consumption has not been elucidated. The main reasons behind this limited information may be (1) the lack studies considering the association of the physiological responses with coffee bioactives in circulation, and (2) the high inter-individual variation observed for the selected cardiometabolic endpoints. Regarding point 1, it should be noted that ascertaining the exact metabolites appearing in circulation after consuming a cup of coffee is a key point to fully unravel the bioactive(s) responsible for its preventive effects. Nevertheless, despite substantial research on caffeine, trigonelline, and phenolic compounds [33], there is a lack of fundamental knowledge on this critical topic, even more when it comes to different patterns of consumption including the number of daily servings and repeated daily doses, which represents a common scenario among coffee consumers. In addition, the circulating metabolites derived from coffee diterpenes [35, 68, 69], potent cholesterol-raising compounds, are still unknown. This information is paramount to draw a more realistic physiological picture and, hence, to better understand the biological properties of long-term coffee consumption [33, 61]. On the other hand, heterogeneity in individual responsiveness to food components (point 2) can obscure associations between diet and health, and limit the understanding of the exact role of the different coffee bioactives. Individual responses to coffee consumption, potentially driven by variations in the bioavailability of key metabolites [70], may be affected by gender [18, 60], age [71], weight or BMI [18, 60], health status [15], genetic polymorphisms [72, 73], smoking [60], physical activity [74], dietary habits, and gut microbiota composition [75–78], among other factors. The gut microbiota has recently emerged as one of the key drivers for diet: cardiometabolic health interactions, due to its ability to produce several metabolites that modulate host physiology at many levels [77, 79, 80]. Likewise, coffee phenolics are highly metabolized by the gut microbiota and are able, in turn, to modulate the microbiota composition [78, 81–83]. This bidirectional relation may deeply condition both the cardiometabolic response and the types and levels of circulating bioactives after coffee consumption.

Attending to the real-life approach of this intervention study, the presence in volunteers’ diets of other sources of phytochemicals cannot be avoided. The intake of amounts of methylxanthines, (poly)phenolic compounds, and trigonelline not provided in the framework of the intervention may thus represent a potential confounding factor for the cardiometabolic outcomes. Three considerations are taken into account to control these variables. First, subjects consuming high amounts of coffee/cocoa bioactives, as assessed by the FFQ provided during the recruitment, will not be enrolled. Second, dietary information collected from the 3-day dietary records, administered in the middle of each intervention period, will be used to verify the information provided by the FFQ. If significant differences are observed among volunteers, the intake of phenolics, methylxanthines, and trigonelline, as assessed by in-house databases, could be used as covariates. Lastly, volunteers will be stratified according to their dietary total antioxidant capacity (TAC) [37] and results for cardiometabolic outcomes will be provided for two separate groups (low and high TAC).

In summary, despite an overwhelming number of published studies, there is a paradoxical lack of knowledge on the bioactives responsible for the observed beneficial effects of coffee, and on their ability to regulate physiological processes involved in its preventive effects. This missing information becomes even more apparent when the effect of dosage and repeated doses during the day are taken into account. Finally, although some factors influencing inter-individual variability have been tackled, most remain still unexplored. This study will try to bridge these major gaps by linking coffee consumption to individual CCDCM profiles and metabolic responses. To do that, in a real-life setting, the design of this study is extremely innovative, joining under the same protocol both acute and short-term observations, maximizing its prospects and reducing all the operational constraints associated with separate intervention studies.

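### Giving cardiometabolic results separately for low- and high-TAC volunteers is a small subgroup analysis, not control of confounding; TAC is better examined as an exploratory treatment-by-TAC interaction in all volunteers

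*Protocol article*

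**What the plan says.** The article's Discussion accepts that phytochemicals from outside the intervention may confound the cardiometabolic outcomes. It then says "Three considerations are taken into account to control these variables". The three are:

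- exclusion of people with high intake at enrolment;
- dietary records kept in the middle of each period, with intake as a possible covariate;
- a split by antioxidant capacity: "volunteers will be stratified according to their dietary total antioxidant capacity (TAC") and "results for cardiometabolic outcomes will be provided for two separate groups (low and high TAC").

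The covariate step is optional. The split is stated without condition. No cut-point or group size is given.

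Under Data and sample collection, TAC is tied to the food frequency questionnaire completed at enrolment. Under Measurements, cardiometabolic markers are secondary endpoints.

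The section on sample size, randomization and statistical analysis plans repeated-measures general linear models, or Friedman tests, with post hoc comparisons, and adds that a P "value <0.05 will be regarded as statistically significant". It mentions no treatment-by-TAC term. Power for the cardiometabolic outcomes is to be worked out only afterwards.

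**The concern.** The split does not do the job it is given. Every volunteer takes all three treatments, so a trait measured once at enrolment has the same value under each treatment and drops out of any within-person contrast. TAC could still modify the treatment effect, but that is a different question. It is answered by estimating how much the effect changes with TAC, not by setting two group-specific results side by side.

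Halving a sample of 21 leaves each group with low power. A pattern of significance in one group and not in the other is then common even when the treatment does the same thing in both. The Discussion names dietary habits among the likely drivers of individual response, so a reader could easily take such a pattern for a real dietary effect. Cutting a continuous score in two also discards information.

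**Working it through.** **Inputs from the article**

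- Difference and completers: "15 subjects will have to complete an acute intervention to detect a change of 600 nmol/h/L^-1".
- Spread: "with a standard deviation of 870 nmol/h/L^-1".
- Error rates: "Keeping a 80% power and an α of 5"%, sidedness not stated.
- Recruitment: "A total of 21 subjects will be recruited to allow for dropouts and for nonparametric statistical analysis (15% additional subjects required").

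**Assumptions made here**

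- 870 is read as the SD of the within-person difference.
- There is one two-sided paired t-test per outcome, and the two groups are independent.
- The TAC split is nearly even: 10 and 11 from 21 volunteers, or 7 and 8 from 15 completers.

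**Step 1. The plan's own figure.** The standardised difference is d = 600/870 = 0.690. Power comes from the noncentral t distribution with n − 1 degrees of freedom and noncentrality d√n. A one-sided 5% test first passes 80% at n = 15 (81.4%), which matches the stated number. Two-sided, the normal approximation gives ((1.960 + 0.842)/0.690)² = 16.5, so 17, and the t-test gives 19. The steps below use the two-sided test.

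**Step 2. Power after the split, at d = 0.690.** This value belongs to a metabolite AUC used to size the primary outcome, so for cardiometabolic markers it is only an illustration.

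| n | Power at d = 0.690 | Effect detectable with 80% power |
|---|---|---|
| 21 | 85.2% | 0.64 SD |
| 11 | 54.2% | 0.94 SD |
| 10 | 49.5% | 1.00 SD |

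**Step 3. Chance that exactly one group is significant when both share the same effect.** With group powers p1 and p2, this is p1(1 − p2) + p2(1 − p1).

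- Groups of 10 and 11: 0.495 × 0.458 + 0.542 × 0.505 = 0.50.
- Groups of 7 and 8 (powers 0.337 and 0.392): 0.337 × 0.608 + 0.392 × 0.663 = 0.465.

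**Step 4. Range without the borrowed effect size.** Here d is set to whatever value gives the whole trial of 21 the stated power.

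| Whole-trial power | Power, n = 10 | Power, n = 11 | Verdicts differ |
|---|---|---|---|
| No effect (5%) | 5% | 5% | 2 × 0.05 × 0.95 = 9.5% |
| 20% | 11.2% | 12.0% | 20.5% |
| 30% | 15.4% | 16.7% | 27.0% |
| 50% | 24.6% | 27.1% | 38.4% |
| 70% | 36.4% | 40.1% | 47.3% |
| 80% | 44.3% | 48.7% | 49.8% |
| 90% | 55.5% | 60.5% | 48.8% |
| 95% | 64.5% | 69.7% | 44.3% |

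About one half is close to the maximum. It applies only when the shared effect is one the whole trial could detect well.

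**Step 5. What an interaction test could do.** For a difference of 0.690 SD between the effects in groups of 10 and 11, the noncentrality is 0.690/√(1/10 + 1/11) = 0.690/0.437 = 1.58 with 19 degrees of freedom. Power is 32%.

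**The case against.** Several stronger readings are tempting, and the article does not support them.

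- **That the two groups will give conflicting verdicts half the time.** This needs a common real effect with roughly 80% whole-trial power. The article gives no effect size, SD or power for any cardiometabolic marker, so a range is all that can be defended.
- **That there will be no interaction test.** None is described, but the full protocol and analysis plan are not shown and may contain one. The article also does not say that group P values will be compared, or that a difference will be inferred from them.
- **That the split replaces the pooled analysis.** The statistical section sets out a general analysis without restricting it to TAC groups, and the Discussion does not withdraw it.
- **That controlling for diet is pointless in a crossover.** Intake outside the intervention can change from one period to the next, and such change does not cancel within a person. The in-period records and the covariate option address that. The criticism here reaches only the fixed enrolment score.

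Two further limits stand. Groups of 10 and 11 presuppose a near-even split and no dropouts. The paired t-test simplifies a planned three-treatment analysis. The split also leaves the primary endpoint untouched.

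These limits reduce the headline figure and the reach of the point. They do not alter what the article commits to: separate results in two small groups, presented as confounder control and not labelled exploratory.

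**Conclusion.** The point holds in limited form. A TAC score fixed at enrolment cannot confound within-person treatment contrasts, so the planned split is a subgroup analysis with little power, and the purpose given for it is mistaken. This conclusion needs no assumed effect size.

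How often separate verdicts would disagree without any true difference does depend on assumptions. It runs from 9.5% with no effect, through 20-38% at 20-50% whole-trial power, to about 50% near 80%. These figures rest on one two-sided 5% paired test per outcome and groups of 10 and 11. They illustrate the problem and are not properties of any named marker. The consequence is confined to the interpretation of secondary endpoints.

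**What to change.** - State that the whole-sample estimate is the main result for each cardiometabolic outcome.
- Examine TAC through a treatment-by-TAC interaction in the model that includes all volunteers, with TAC continuous and taken from the enrolment questionnaire. Report the interaction estimate with its 95% CI and label it exploratory.
- Show the low- and high-TAC groups descriptively, without tests inside each group.
- Describe TAC as a possible effect modifier, not as a means of controlling confounding.
- Keep the in-period dietary records as possible covariates.

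The cost is a change of wording and a little more analysis; no new data are needed. The drawback is the interaction test's low power, about 32% in the illustration above. A non-significant interaction must not be read as evidence that the effect is the same at all levels of TAC; the interval should carry the interpretation.
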